## Background

Hypertonic Saline provides an alternative to large volume time limited resuscitation to restore hemodynamic stability and minimize the posttraumatic organ dysfunction. There is however, no clear clinical evidence supporting the hypothesis that hypertonic saline is the optimal choice for prehospital trauma resuscitation, specifically with respect to brain injury. Most of the current evidence demonstrating anti-inflammatory and immunological properties of hypertonic saline comes from experimental models (animal and isolated cell preparations) and remains untested in humans. A recent meta-analysis demonstrated that hypotensive patients with severe head injury are twice as likely to survive if resuscitated with hypertonic saline in dextran (HSD) compared with isotonic crystalloids [1] In separate clinical trials, HSD resuscitation was associated with a reduced incidence of acute respiratory distress syndrome (ARDS), renal failure and infectious complications [2-4]. Because of the compelling current evidence suggesting the effectiveness of HSD and the known burden of traumatic brain injury (TBI) and multiorgan dysfunction, this question requires direct evaluation.

The application of rigorous clinical trial methodology in the prehospital setting requires overcoming a number of challenges unique to the setting. We conducted a feasibility study prior to implementing a larger randomized clinical efficacy trial. This feasibility study is significantly different from other prehospital trauma trials because it is designed by investigators from multiple disciplines including immunology, neurology, surgery, anaesthesia, neuropsychology and neuroimaging to address aspects of TBI not evaluated previously and employs a randomized clinical trial design and waiver of consent. In addition to the primary study objective of survival at 30 days we plan to evaluate circulating and cellular immunomodulation within the first 24 hours, neurocognitive and neuropsychological testing at 4 and 12 months, and structural damage through MRI scanning up to 4 months post trauma.

We report the methods in detail and have appended the data collection tools and case report forms for this feasibility study. All case report forms and data collection forms were created by the investigators as prior forms did not exist previously in the literature.

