### Intervention Protocol

All patients will be treated according to research medical directives (Additional File 2) based on a standardized provincial out of hospital trauma treatment protocol [6]. The study solution is started within 4 hours of the time the emergency call was received at ambulance dispatch. Samples of peripheral blood will be collected upon emergency department (ED) arrival, 12, 24 and 48 hours after ED arrival from a vein remote from the venous access site for the study infusion. Blood samples will be collected in heparinized and non-additive vacutainers by a single trained lab technician and immediately (within 1-h) shipped to a single designated laboratory for whole blood flow cytometric cellular analyses and measurement of circulating molecular immuno-inflammatory markers. Serum will be frozen for subsequent analyses. Whole blood will be incubated with saturating concentrations of the adhesion (CD62L-FITC, CD11b-PE), degranulation (CD66b-FITC, CD63-PE), apoptotic/necrotic (Annexin V-PE, 7-AAD, Active Caspase-3, CD95-Fas, CD178-FasL) markers, in conjunction with CD14-APC surface staining (to differentiate leukocyte subsets). Results will be acquired on a Becton Dickinson dual-laser (488 nm and 635 nm) BD FACSCalibur flow cytometer using CellQuest software. Serum samples will be analyzed for pro-/anti-inflammatory cytokines (TNF-α, IL-10), soluble leukocyte and endothelial-derived adhesion molecules (sICAM-1, sVCAM-1, sE-selectin, sL-selectin), pro-/anti-apoptotic molecules (sCD95, sCD95L, TNF-RI, sFas/FasL) and neuro-biomarkers of brain injury (S100B, NSE, MBP) (Additional File 3).

Magnetic Resonance Imaging on a 1.5 Tesla General Electric Signa Magnet is planned for completion at 4 months for consenting patients using a standardized protocol (Additional File 4, 5, 6, 7); a 3D 1.3 mm thick, T1-weighted, series (TE 4-2, TR 35, flip angle 35), an interleaved 3 mm thick PD and T2-weighted spin echo sequence (TE 39/80, TR 3000, flip angle 90) (Additional File 6), a gradient echo sequence and Diffusion Tensor Imaging (11 directions) (Additional File 7); tissue segmentation and parcellation including lesion quantification [7-12] using previously published in-house software as well as ANALYZE software [7,13].

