#### Neurocognitive Outcomes

At discharge:

• Cerebral Performance Category [14]

At 4 months:

• Functional Independence Measure (FIM)[15]

• Disability Rating Scale (DRS) [16-19]

• Glasgow Outcome Scale (GOS)[16,20,21]

• Glasgow Outcome Scale Extended (GOS Extended)[16,20]

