#### Neuropsychological Outcomes

At 4 months:

• Learning and Memory

○California Verbal Learning Test[22]

○Wechsler Memory Scale-Revised Immediate and Delayed Visual Reproduction[23]

○Rey-Osterreith Immediate and Delayed Memory[24]

• Working Memory

○WMS-R Backward Digit Span[23]

• Executive Function

○FAS Verbal Fluency[25]

○Wisconsin Card Sorting Test[26]

○Trail Making Test Parts A & B[27]]

○Stroop Test[28]

○Object Alternation[29]

○WMS-R Forward Digit Span[23]

• Language Function

○Boston Naming Test[27]

○Semantic Fluency[25]

• Visuospatial Function

○Judgment of Line Orientation[30]

○Facial Recognition[30]

• Speed of Processing

○WAIS-R Digit Symbol[31]

○Trail Making Test Part A[27]

• Beck Depression Scale[32].

A focused attention reaction time test[33,34] with varying levels of complexity will be administered at 12 months.

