### Analysis Plan

This is a feasibility study of two year's duration with a projected screening of 130 patients and recruitment of 100. The primary outcome measure, change in the proportion surviving 30 days post trauma between the treatment and control groups, will be analyzed by means of a generalized linear mixed model which included covariates of interest. The two groups are not expected to be different at baseline, and it is hypothesized that the treatment group would show a 20% decrease in mortality at 30 days post trauma whereas the control group would remain unchanged. To derive a reduced subset of risk factors for the predictor models, acceptable model building strategies are planned (i.e. dropping variables showing extremely small variability and those found to be highly correlated (i.e. correlation coefficient ≥0.8)). Treatment and time factors will be analyzed using a generalized linear mixed models of the secondary outcome repeated measures: the change in mortality after discharge over time as well as the neurocognitive and neuropsychological outcome summary scores. For secondary outcome analyses, the alpha will be adjusted to account for multiple comparisons. Where there is more than one measure for a neuropsychological test (e.g., processing speed, working memory, visuospatial, language, verbal memory, non-verbal memory - with the exception of executive processes, since different measures relate to different brain regions), a composite or prototypical measure will be derived from group comparison. Serial changes in all secondary immune modulation measures, neuro-biomarkers, neurocognitive and neuropsychological outcomes, and structural imaging measures will be evaluated by two-way ANOVA for repeated measures. All analysis will be conducted blinded to treatment assignment.

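### Models with a time factor are fixed for neurocognitive, neuropsychological and MRI outcomes that the outcome lists schedule once, and the first two families are given two models with no ranking

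*Protocol article*

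**What the plan says.** The Analysis Plan of the protocol article sets two analyses for overlapping outcomes.

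- The first is a mixed model: "Treatment and time factors will be analyzed using a generalized linear mixed models of the secondary outcome repeated measures". The outcomes named for it are "the change in mortality after discharge over time as well as the neurocognitive and neuropsychological outcome summary scores".
- The second comes later in the same paragraph. It concerns serial changes, and its list runs from immune measures and neuro-biomarkers to "neurocognitive and neuropsychological outcomes, and structural imaging measures will be evaluated by two-way ANOVA for repeated measures".

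Structural imaging appears under the ANOVA only. The neurocognitive and neuropsychological outcomes appear under both, and no sentence says how the two analyses divide the work or which result is to be reported.

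The schedule is given elsewhere.

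- **Neurocognitive Outcomes:** the Cerebral Performance Category (CPC) at discharge. FIM, DRS, GOS and the extended GOS appear under the 4-month heading.
- **Neuropsychological Outcomes:** the whole battery, including the Beck Depression Scale, at 4 months. One further test follows: "A focused attention reaction time test[33,34] with varying levels of complexity will be administered at 12 months".
- **Intervention Protocol:** MRI "is planned for completion at 4 months for consenting patients using a standardized protocol".
- **Background:** "neurocognitive and neuropsychological testing at 4 and 12 months, and structural damage through MRI scanning up to 4 months post trauma".

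**The concern.** A time factor needs the same quantity measured on the same patient at two or more times. The instrument-level lists give one time per instrument, so the analysis named for these outcomes does not match the data that the lists say will be collected.

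Two things are at stake. First, the effect of the intervention on neurocognitive, neuropsychological and brain-structure outcomes is a stated secondary objective, yet its interaction with time, which is what an analysis of serial change would report, is undefined on the listed schedule. An analyst who tried to create a time axis would have to line up the discharge category, the 4-month scales and the 12-month reaction time, which are different instruments on different scales.

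Second, two models for one outcome family leave it open after the data are seen which result is reported. If some tests are repeated, the choice could matter. A classical repeated-measures ANOVA uses only patients with every time point, while a mixed model also uses those with partial data. The article's Discussion expects many patients to be lost to follow-up, so the two could rest on different sets of patients.

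**Working it through.** The plan gives no figure to reproduce here. The check compares the listed schedule with what the named models need.

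**Step 1: count the instruments and their times.**

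| Family | Distinct instruments | Listed time | Listed at two times |
|---|---|---|---|
| Functional scales (CPC, FIM, DRS, GOS, extended GOS) | 5 | CPC at discharge; other four at 4 months | 0 |
| Neuropsychological battery | 16 | 4 months | 0 |
| Reaction time test | 1 | 12 months | 0 |
| MRI measures | not counted | 4 months | none listed |

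The neuropsychological list has 18 entries including reaction time. Trail Making Part A appears in two domains, so 18 − 1 = 17 are distinct (16 + 1). The total is 5 + 17 = 22, of which 0 are listed at two times. Immediate and delayed recall parts of a memory test are listed under the single 4-month heading and do not create a second visit.

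**Step 2: degrees of freedom.** For two arms, N patients and T time points, a two-way repeated-measures ANOVA has

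- time: T − 1
- treatment by time: (2 − 1)(T − 1)
- within-patient error: (N − 2)(T − 1)

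N = 100 is the planned recruitment in the Analysis Plan. It is an upper bound, because deaths and losses will lower it.

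| Schedule | T | Time | Treatment × time | Within-patient error (at most) |
|---|---|---|---|---|
| Outcome lists and MRI, as printed | 1 | 0 | 0 | 98 × 0 = 0 |
| Background, if the same tests are repeated at 12 months | 2 | 1 | 1 | 98 × 1 = 98 |
| Biomarkers (arrival, then 12, 24 and 48 hours) | 4 | 3 | 3 | 98 × 3 = 294 |

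At T = 1 every term involving time vanishes. What remains is a between-arm comparison with 1 degree of freedom for treatment and at most 98 for error. The mixed model's time and treatment-by-time effects disappear for the same reason.

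**Step 3: does the Background settle the schedule?** It promises "neurocognitive and neuropsychological testing at 4 and 12 months" but names no instrument. The sentence can be met in two ways: by the 4-month battery plus the separate 12-month reaction time test, with nothing repeated; or by repeating some tests, which the outcome lists do not show. On the first reading T = 1 throughout. On the second the Background and the outcome lists disagree. Neither reading tells an analyst which instruments carry a time factor. For MRI, the Background's wording could allow an earlier scan, but the Intervention Protocol plans one at 4 months and no other study scan is listed.

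**The case against.** The strongest reply has four parts.

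1. **The models may be estimable.** If the Background means that the same tests are given at 4 and 12 months, T = 2 and both models can be fitted. This stands. A reader might infer from the outcome lists that neither analysis can be run at all, but the document does not support that. It leaves the schedule in doubt, and it plainly supports the ANOVA for biomarkers. Even at T = 1 the treatment effect can still be estimated.

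2. **The two models may not conflict.** One sentence refers to summary scores and the other to serial changes, so a division between composites and individual measures is possible. A repeated-measures ANOVA is also closely related to a linear mixed model with a patient effect. It would therefore be too strong to call the analyses incompatible. But the division is not stated, and the choice of reported result stays open.

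3. **The article is condensed.** A full visit schedule may lie in appended forms or a separate plan. This limits certainty that nothing is repeated. It does not excuse the mismatch, because the article itself states both the models and the times, and they do not fit together.

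4. **The outcomes are secondary.** The primary objective is feasibility: survival rates for planning, randomization compliance, ease of implementation and adverse events. None of these depends on the disputed analyses. This stands and limits the severity.

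**Conclusion.** The point holds in a limited form. On the listed schedule, none of the 22 neurocognitive and neuropsychological instruments is listed at two times, and MRI is planned once. The time and treatment-by-time effects fixed for these outcomes therefore have 0 degrees of freedom. The Background leaves it unclear whether any test is repeated. The neurocognitive and neuropsychological families also have two models and no statement of which counts.

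The conclusion assumes that the outcome sections give the intended schedule by instrument. If the same tests are repeated at 12 months, the time effects can be estimated for those tests, and what remains is a contradiction in the schedule and an unranked pair of models. Biomarkers are unaffected, and the point does not extend to mortality. Severity is moderate: secondary outcomes of a feasibility trial, correctable before analysis.

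**What to change.** 1. **Settle the schedule first.** Reconcile the Background with Neurocognitive Outcomes and Neuropsychological Outcomes by stating which instruments, if any, are repeated at 12 months. State in the same place that MRI is done once, if that is so.
2. **Outcomes measured once.** Replace the repeated-measures analysis with one between-arm comparison at the scheduled time, with a 95% CI and a method suited to the scale. Ordinal regression would be one option for CPC, GOS and the extended GOS. The list should cover every once-measured outcome, including GOS, the Beck Depression Scale, the executive measures that are kept out of the composites, and the MRI measures.
3. **Instruments measured at two or more times.** Name a single longitudinal model. The mixed model already in the plan is preferable, because it uses patients with partial data and many losses are expected.
4. **Biomarkers.** No change is needed on this point.

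The cost is wording in the Analysis Plan and, depending on step 1, in the Background or the outcome lists. No new data are needed if no repeat was intended. The plan gives up a claim about change over time for outcomes measured once.

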### Study outcomes

#### Survival

The primary clinical outcome is survival at 30 days.

Secondary clinical outcomes are survival at 48 hours and to hospital discharge.

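### The one secondary mortality analysis in the plan is of mortality after discharge, treated as a repeated measure; the declared secondary outcomes are survival at 48 hours and to discharge

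*Protocol article*

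**What the plan says.** Under Study outcomes, Survival, the protocol article sets the primary outcome ("The primary clinical outcome is survival at 30 days") and then states: "Secondary clinical outcomes are survival at 48 hours and to hospital discharge". No survival outcome after discharge is listed there.

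The Analysis Plan covers the primary outcome as the "change in the proportion surviving 30 days post trauma between the treatment and control groups", using a generalized linear mixed model with covariates. For secondary outcomes it says: "Treatment and time factors will be analyzed using a generalized linear mixed models of the secondary outcome repeated measures". It then names what those repeated measures are: "the change in mortality after discharge over time as well as the neurocognitive and neuropsychological outcome summary scores". This is the only secondary mortality analysis that the article describes.

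**The concern.** There are three difficulties.

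- **Wrong outcome.** The declared secondary survival outcomes end at or before discharge. The variable named for analysis starts at discharge.
- **Ill-fitting model.** Mortality is grouped with neurocognitive and neuropsychological scores. A score can rise or fall within a patient from visit to visit. Death occurs once and is final.
- **Selected population.** On its plain meaning, mortality after discharge can be observed only in patients discharged alive. Survival to discharge is itself a trial outcome, and the trial's hypothesis is that treatment lowers early mortality. If it does, treatment helps to decide who enters this analysis, and the comparison loses the protection of randomisation.

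At stake is the secondary survival evidence. The first feasibility objective is to obtain survival rates by arm for planning a definitive trial, and survival at 48 hours and to discharge would inform that planning directly.

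**Working it through.** The plan states no figure for this analysis, so there is nothing to reproduce. The check is a comparison of text, followed by an illustration under assumed rates.

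**Step 1: the two sections side by side**

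| | Study outcomes, Survival | Analysis Plan |
|---|---|---|
| Primary | Survival at 30 days | Proportion surviving 30 days post trauma |
| Secondary | Survival at 48 hours; survival to discharge | Change in mortality after discharge over time |

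The primary row agrees. The secondary row does not: neither declared outcome appears in the right-hand column, and the variable that does appear is not declared.

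**Step 2: the model.** Once a patient has died, every later value is fixed. A repeated-measures model of alive/dead status therefore has no within-patient change to estimate in the way it has for a test score. A discrete-time hazard model, restricted at each interval to patients still at risk, would be legitimate, but the text does not describe one.

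**Step 3: how many deaths would be left out on the literal reading.** The only documented input is the recruitment target of 100 ("projected screening of 130 patients and recruitment of 100"). The in-hospital death rate *h* and the later death rate among discharged patients *p* are assumptions.

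- Patients contributing = 100 × (1 − h)
- Later deaths = 100 × (1 − h) × p
- Share of deaths omitted = 100h ÷ [100h + 100(1 − h)p]

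| h | p | Contributing | Later deaths | Deaths omitted |
|---|---|---|---|---|
| 25% | 2% | 75 | 1.5 | 25 ÷ 26.5 = 94% |
| 25% | 5% | 75 | 3.75 | 25 ÷ 28.75 = 87% |
| 40% | 2% | 60 | 1.2 | 40 ÷ 41.2 = 97% |
| 40% | 5% | 60 | 3.0 | 40 ÷ 43 = 93% |

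The analysis would use 60-75 of 100 patients and about 1-4 deaths, and would omit 87-97% of all deaths. With wider assumptions (h of 20-50%, p of 2-10%) the omitted share runs from 20 ÷ 28 = 71% to 50 ÷ 51 = 98%.

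**Step 4: can the selection mislead?** The plan hypothesises that "the treatment group would show a 20% decrease in mortality at 30 days post trauma", without saying whether this is relative or absolute. For illustration, take a 20% relative reduction in in-hospital mortality from an assumed 40% to 32%. Assume later mortality of 3% in patients who would be discharged under either treatment, and 25% in those alive at discharge only because of treatment.

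- Control: later mortality among discharged patients = 3%; overall mortality = 0.40 + 0.60 × 0.03 = 41.8%.
- Treatment: discharged = 68%; later deaths = 0.60 × 0.03 + 0.08 × 0.25 = 0.038; later mortality among discharged patients = 0.038 ÷ 0.68 = 5.6%; overall mortality = 0.32 + 0.038 = 35.8%.
- Odds ratio for death after discharge = (0.0559 ÷ 0.9441) ÷ (0.03 ÷ 0.97) = 1.91, against treatment.

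Treatment saves lives overall in this example, yet looks harmful after discharge. With in-hospital control mortality of 30-50% and later mortality of 10-40% in the patients saved, the odds ratio runs from about 1.2 to 3.3. The example shows that the direction can reverse, not that it will.

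**The case against.** The strongest counter-case is that the text is being read harder than it can bear.

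- **No exclusion is stated.** A reader might infer that the plan drops in-hospital deaths. The Analysis Plan defines no population for this analysis, and its wording could mean cumulative vital status at assessments after discharge, with earlier deaths counted. This stands as a caution: Steps 3 and 4 apply only to the literal reading. The looser reading would ease the selection problem, but would cure neither the mismatch of outcomes nor the poor fit of a repeated-measures model.
- **No model structure is stated.** A reader might infer a patient-level random effect with a treatment-by-time interaction and call the model meaningless. The plan mentions only treatment and time factors, so that structure cannot be attributed to it. What can be said is that mortality is labelled a repeated measure and the label does not suit it.
- **A journal article condenses.** Silence on the method for two simple binary outcomes is ordinary and is not the point here. The point is that the article does name a secondary mortality analysis, and names it for a different outcome.
- **The trial's main results do not depend on it.** This also stands. The primary analysis is anchored to trauma, not discharge, and counts in-hospital deaths up to day 30. None of the four feasibility objectives rests on this secondary model.

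**Conclusion.** The point holds at moderate severity. The contradiction between the two sections and the unsuitable label for mortality rest on the text alone and need no assumption. The possible bias in the comparison of arms rests on the literal reading, under which only patients discharged alive contribute.

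The figure of 87-97% of deaths omitted also needs the assumed rates of 25-40% in-hospital and 2-5% later mortality, which have no source in the documents. A reader might go further and conclude that the trial as a whole ignores most deaths, or that the later-mortality model cannot be estimated. The documents support neither: the 30-day analysis is untouched, and no rate is given from which the number of later deaths could be predicted.

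**What to change.** 1. Remove mortality from the repeated-measures model and keep that model for the outcome scores.
2. State that survival at 48 hours and survival to discharge are analysed in all randomised patients, as proportions by arm with 95% confidence intervals and a risk difference. They remain within the multiplicity statement already made ("For secondary outcome analyses, the alpha will be adjusted to account for multiple comparisons").
3. If mortality beyond discharge is wanted, add it to the Survival outcomes. Analyse it from randomisation in all randomised patients with in-hospital deaths counted, for example as time to death censored when last known alive.

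Items 1 and 2 change wording only, since the outcomes are already declared. Item 3 has a small cost: it needs dates of death and of last contact. The article does not confirm that these are collected, and its Discussion expects patients to be lost after discharge. Availability should be checked against the case report forms before item 3 is adopted.

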## Abstract

**Background:**

Clinical trials evaluating the use of hypertonic saline in the treatment of hypovolemia and head trauma suggest no survival superiority over normal saline; however subgroup analyses suggest there may be a reduction in the inflammatory response and multiorgan failure which may lead to better survival and enhanced neurocognitive function. We describe a feasibility study of randomizing head injured patients to hypertonic saline and dextran vs. normal saline administration in the out of hospital setting.

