### Cellular and Molecular Biomarkers

Whole blood and circulating immuno-inflammatory markers will be measured on hospital arrival and at 12, 24 and 48 hours later

• Total leukocyte count and differential; neutrophil and monocyte surface expression of cellular adhesion molecules and degranulation markers: L-selectin (CD62L) and β_2_-integrin (CD11b) [36]

• Leukocyte apoptotic/necrotic surface and intracellular markers (Annexin V-PE, 7-AAD, Active Caspase-3, Fas (CD95), FasL (CD178) [37-42]

• Soluble pro-/anti-apoptotic molecules (sCD95, sCD95L, TNF-RI, sFas/FasL)[43]

• Leukocyte and endothelial-derived serum soluble adhesion molecule concentrations: intercellular adhesion molecule-1 (sICAM-1), vascular adhesion molecule-1 (sVCAM-1), sE-selectin, sL-selectin [44-46]

• Pro and anti-inflammatory cytokine expression: tumour necrosis factor (TNF)-α, and interleukin (IL)-10 [37,47,48];

• PT/PTT, tissue factor (TF), thrombomodulin (TM), fibrinogen, platelet count and Hg; Ionized calcium, and pH [49]

• Serum sodium, chloride and osmolarity

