Finally, we anticipate two types of patients will provide unique challenges to data collection: those who die in the Emergency Department and those who met the Glasgow Coma Scale criteria for enrolment however this finding was attributed to drugs or alcohol rather than brain injury and they were discharged from the Emergency Department within hours of the accident. Strategies are in place to address these issues a priori in advance of the trial. Those who die soon after arrival in the Emergency Department often require the coroner's intervention and traditionally the charts are instantly sequestered by the coroner's staff. They commonly are unidentified and therefore it will be hard to find their health care advocate who can consent to using their blood and outcome data up until their death. We hope to overcome this with an agreement in principle with the provincial coroner to allow access to the chart at the coroner's office. We have developed a working practice with the coroner's office to confirm identification and next of kin data at the time of body retrieval

We anticipate the patients who met the GCS eligibility criteria based on alcohol consumption and are discharged relatively quickly from the Emergency Department will be hard to track down. There will be insufficient time to identify them correctly or confirm their demographic information and next of kin prior to discharge and follow up of the non brain injured group will be challenging. We will use a hierarchical approach to find these patients including government health care billing number, police report, Emergency Department report, Ambulance call report, web based telephone listings, newspapers which identify the individual based on the notoriety of the event. In addition, each receiving hospital had an active trauma registry which tracked the patients to conduct a functional evaluation at 30 days post-discharge. The surgical investigators have offered to confirm identification and obtain consent in their outpatient clinics if the patients return for follow up. This may prove to be helpful as many of these patients require forms completed by the physician for return to work, disability, insurance etc.

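### Repeated-measures ANOVA of serial changes suits the blood markers poorly: the first sample is post-treatment, and early deaths and discharges leave incomplete series

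*Protocol article*

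**What the plan says.** The relevant statements in the protocol article are these.

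- **Treatment.** The Abstract describes randomizing to "hypertonic saline and dextran vs. normal saline administration in the out of hospital setting". Under Intervention Protocol, "The study solution is started within 4 hours of the time the emergency call was received at ambulance dispatch".
- **Sampling.** The same section states: "Samples of peripheral blood will be collected upon emergency department (ED) arrival, 12, 24 and 48 hours after ED arrival". Cellular and Molecular Biomarkers repeats the schedule: "Whole blood and circulating immuno-inflammatory markers will be measured on hospital arrival and at 12, 24 and 48 hours later". No sample before treatment is listed.
- **Analysis.** The Analysis Plan takes "Serial changes in all secondary immune modulation measures, neuro-biomarkers, neurocognitive and neuropsychological outcomes" together with imaging, and ends the sentence: "structural imaging measures will be evaluated by two-way ANOVA for repeated measures". Earlier in the same section, generalized linear mixed models are named for other repeated secondary outcomes.
- **Incomplete series.** The Discussion expects difficulty with "those who die in the Emergency Department and those who met the Glasgow Coma Scale criteria for enrolment". It says of the second group, whose low score was due to drugs or alcohol, that "they were discharged from the Emergency Department within hours of the accident".

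**The concern.** The effect of HSD on the immuno-inflammatory response is the first secondary objective listed, with neuro-biomarkers beside it. Two features of the planned analysis work against estimating it.

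1. Change measured from a post-treatment sample is not change from baseline. If HSD acts quickly, part or all of its effect is already in the first value and is subtracted out.
2. A method that needs all four samples restricts the analysis to patients still alive and sampled at 48 hours. Survival to 48 hours is itself a secondary outcome, so this group is selected after randomization by something treatment may affect.

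The risk is that a study meant to inform a definitive trial reports no marker effect, or a misleading one, because of the contrast and the analysis set.

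**Working it through.** The article gives no effect size, SD, power or loss rate for the markers, so there is no figure to reproduce. The algebra below needs no outside input. The simulations rest on assumptions, which are stated.

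**Step 1: what change from arrival estimates.** Let δ(t) be the difference in mean marker level, HSD minus control, at time t.

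- Difference in change from arrival to 48 h = δ(48) − δ(0).
- Group main effect = [δ(0) + δ(12) + δ(24) + δ(48)] / 4.

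Suppose the shift at arrival is d:

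- It persists to 48 h: change difference = d − d = 0.
- It fades to nothing by 48 h: change difference = 0 − d = −d, the opposite sign.

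If the shift is d at all four times, the main effect is 4d/4 = d. The early shift does not cancel it.

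**Step 2: illustration of the loss of power.** Assumed: 50 patients per arm (the projected 100, split equally), four times, SD 1, within-patient correlation 0.6, true effect −0.5 SD at 12, 24 and 48 h, two-sided 5% level, complete data, 4,000 simulated trials per row.

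| Effect at arrival (SD) | Change difference, arrival to 48 h (SD) | Power, treatment-by-time | Main effect (SD) | Power, main effect |
|---|---|---|---|---|
| 0 | −0.50 | 83% | −0.38 | 61% |
| −0.125 | −0.38 | 57% | −0.41 | 67% |
| −0.25 | −0.26 | 27% | −0.44 | 73% |
| −0.375 | −0.12 | 10% | −0.47 | 80% |
| −0.5 | 0.00 | 5% | −0.51 | 85% |

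The first row agrees with the formula: (0 − 0.5 − 0.5 − 0.5)/4 = −0.375.

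**Step 3: patients left with complete series.** If 10%, 20%, 30% or 40% of 100 patients lack at least one sample, 90, 80, 70 or 60 remain. As an example of how loss accumulates, assume 80% are alive and in hospital at 48 h. If each of the three later samples is then obtained 90% of the time, 0.80 × 0.9³ = 58% are complete; at 95% it is 0.80 × 0.95³ = 69%. The 80%, 90% and 95% are assumptions.

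**Step 4: when that loss biases the comparison.** Same set-up, with loss concentrated in patients with higher underlying marker levels and only complete series analysed.

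| True effect (SD) | Loss, control / HSD | Estimated main effect (SD) | Main-effect test significant |
|---|---|---|---|
| 0 | 20% / 20% | 0.00 | 8% |
| 0 | 20% / 10% | +0.10 | 12% |
| 0 | 30% / 10% | +0.19 | 23% |
| 0 | 40% / 20% | +0.19 | 20% |
| −0.5 at all times | 20% / 20% | −0.50 | 83% |
| −0.5 at all times | 30% / 10% | −0.30 | 44% |

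Equal loss gave no bias. In these runs the change contrast was not biased by loss, because loss was tied to a patient level that is constant over time. So under these assumptions the early shift weakens the treatment-by-time term and unequal selective loss biases the main effect. Neither term of the ANOVA is protected against both.

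**The case against.** A reader might infer that the plan drops patients without all four samples and that the treatment effect is therefore distorted. The documents do not say this. There is no exclusion or complete-case rule, and handling of missing data may sit in a fuller plan that is not shown. Ethical Considerations seeks consent to analyse blood results of everyone randomized, and the Discussion wants to use data on early deaths up to the time of death. That suggests partial series are meant to count.

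Nor does the article call the arrival sample a baseline or select change from arrival as the contrast. Serial changes by two-way ANOVA may mean levels over time by group, and that analysis contains a main effect which an early shift leaves intact. Bias from loss needs loss that differs by arm and is related to the marker, and the documents give no rate for either arm. The 4-hour window is an upper limit that applies to both arms, so variation in time since infusion would mainly add noise. These are also secondary, exploratory measures in a feasibility study.

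All of this stands, and it makes the point conditional. It does not remove it. The article names both the method and the target, so the objection is to a stated choice and not to silence. If partial series are meant to be used, the classical form of the named method cannot use them.

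**Conclusion.** The concern holds in conditional form. The arrival sample follows the start of treatment, so any change-from-arrival or treatment-by-time contrast can hide an early effect, or reverse it if the effect fades. In its classical form the named ANOVA keeps only complete series, although the article itself expects early deaths and discharges. The certain cost is precision; bias arises only with loss that is both unequal between arms and related to the marker.

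The size of either effect cannot be derived from the documents. The simulated figures show direction and plausible scale under assumed inputs and are not estimates for this trial. The article also does not say whether the infusion is complete at the first draw, so how much effect is present by then is unknown. The change is worth making because it is cheap and a better-suited class of model is already in the plan.

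**What to change.** For the blood markers, amend the Analysis Plan as follows.

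- Replace the two-way repeated-measures ANOVA with a likelihood-based mixed model with terms for treatment, time and treatment-by-time, using every available sample. The section already uses mixed models for other repeated outcomes.
- Define the ED-arrival sample as the first post-treatment outcome, not as a baseline or reference value.
- Report the arm difference in level, with its confidence interval, at arrival, 12, 24 and 48 hours.
- State that results at later times are conditional on being alive and sampled, and present them beside 48-hour survival by arm.

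While the sentence is being edited, settle which method applies to the neurocognitive and neuropsychological outcomes, which the same section assigns both to a mixed model and to the ANOVA.

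The cost is analysis wording and slightly more analysis work, with no new samples or visits. One limit remains. The model assumes that missing values are missing at random, and this does not resolve truncation by death, since a marker has no value after death.
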